## Abstract

**Background::**

Acupuncture has been widely used to treat primary dysmenorrhea (PD) with satisfactory outcomes. Sanyinjiao (SP6) is the most commonly used acupoint for PD. Different needling techniques may influence the effect of SP6, and its underlying mechanism needs to be explored. This randomized controlled parallel trial is designed to evaluate the immediate analgesic effect and hemodynamic responses in uterine arterial blood flow of perpendicular needling and transverse needling at SP6 in patients with PD of cold-dampness stagnation pattern using color doppler ultrasonography.

**Methods::**

Forty-eight patients who meet inclusion criteria will be randomized in a ratio of 1:1 to either perpendicular needling or transverse needling groups. Every participant will receive 1 session of acupuncture treatment for 10 minutes at bilateral SP6. In the perpendicular needling group, needles will be inserted vertically 1 to 1.2 cun and will be manipulated to achieve needling sensation. In transverse needling group, the needles will be inserted transversely 1 to 1.2 cun toward the abdomen without any manipulation to avoid needling sensation. Color doppler ultrasonography will be performed before, during, and after needling. The primary outcome measure is visual analog scale for pain. The secondary outcome measures include the uterine artery blood flow changes by measuring pulsatility index, resistance index values, and ratio of systolic peak and diastolic peak, the Hamilton anxiety scale, blood pressure, and heart rate. Adverse events in both groups also will be recorded.

**Discussion::**

This trial will be the first study protocol designed to explore the influence of needling techniques on the analgesia effect of solo acupoint and its hemodynamic responses for PD. It will promote more widespread awareness of the benefits of using suitable needling techniques in acupuncture clinical setting and provide a further explanation of the underlying hemodynamic mechanism.

**Trial registration::**

This study protocol was registered at the Chinese clinical trial registry (ChiCTR1900026051).

## Introduction

1

Dysmenorrhea is defined with abdominal pain, which usually happens just during or before menstruation period.^[1,2]^ It has been reported as a most common gynecologic complaint, with a prevalence between 16% and 91% worldwide.^[3]^ Approximately 65% cases occur in USA,^[4]^ 60% in Canada,^[5]^ while 41.7% in China.^[6]^ Although dysmenorrhea is not life-threatening, it can restrict social and daily routine works in young women,^[7]^ decrease quality of life,^[7,8]^ reduce daily learning and educational activities, and reduce attending at school.^[9]^ Moreover, severe dysmenorrhea may lead to miss of 600 million working hours and loss of $2 billion in productivity annually.^[10]^ The first line treatment option for relieving pain in PD is nonsteroidal antiinflammatory medications,^[11]^ however their side effects including gastro-intestinal disorders, kidney or liver injury are problematic.^[12]^ Therefore, more effective and safe therapies are desired by both doctors and patients.

Acupuncture has been widely accepted for treatment of dysmenorrhea in China for thousands of years^[13]^ and has been gradually recognized as a complementary therapy for PD in a Cochrane review^[14]^ and metaanalysis^[15,16]^ in modern society as well. Different acupuncture-related methods are used for relieving dysmenorrhea, including body acupuncture, ear acupuncture, moxibustion, cupping, injection,^[17]^ and acupressure.^[11]^ Sanyinjiao (SP6) acupuncture point, the intersecting point of liver, kidney and spleen channels, is closely related to the uterus.^[18]^ In the clinical practice of acupuncture, SP6 is found to be one of the most commonly used points for PD with satisfied pain-relief effect,^[19–25]^ particularly in patients with cold-dampness stagnation pattern.^[26]^

According to classic Chinese acupuncture theory, applying proper needling technique, particularly the depth, angle, and direction of the needling at an acupoint, is an essential point which may contribute to the results of acupuncture. Our previous study showed that perpendicular deep needling at SP6 to induce strong needling sensation had better pain-relief effect for PD patients compared to perpendicular superficial needling.^[27]^ However, many patients particularly in western countries did not like needling sensation, and their attitude might affect the manipulation of the acupuncturists.^[28]^ Transverse needling has advantage of less pain, and easy to be accepted in large number of patients who are afraid of needling sensation. One study showed that transverse superficial needling at SP6 on PD is better than that of oral administration of indomethacin enteric-coated tablets.^[29]^ We also found^[30]^ that transverse superficial needling at SP6 had similar significant immediate analgesic effect in PD patients as perpendicular deep needling. However, the underlying mechanism of pain-relief effect of transverse needling remains unclear and worthy of further study.

Studies showed that the menstrual pain is closely related to the decreased uterine blood flow,^[31]^ and a high resistance against blood flow in the uterus was found in doppler indices.^[32]^ Our previous study showed that although perpendicular needling at SP6 could immediately relive menstrual pain, it did not show the effects on uterine arterial blood flow in PD patients.^[23]^ Another animal study revealed that transverse needling had analgesia effect through decreasing prostaglandin (PG) F2α, increasing β-endorphin, nitric oxide, and substance P to relieve uterine cramps, increase blood flow.^[33]^ Therefore, we hypothesized that compared with perpendicular needling, the analgesia effect of transverse needling at SP6 may be achieved by better improving uterine arterial blood flow.

This study is designed to investigate the immediate analgesic effect and uterine arterial blood flow changes of transverse needling at SP6 versus perpendicular needling for treatment of PD.

## Methods

2

### Design and setting

2.1

A prospective randomized, patient-assessor-blinded, controlled trial was designed in Beijing University of Chinese Medicine (BUCM) and will be conducted in 3rd affiliated hospital of BUCM, China from September 30 2019 till July 31 2020. Participants who meet the diagnostic criteria for PD of the consensus guideline,^[11]^ and cold–dampness stagnation pattern according to a revised Chinese national guide line^[34]^ will be randomly allocated in a ratio of 1:1 to either perpendicular needling group or transverse needling group. This study protocol has been approved by the supervision of the ethics committee of the 3rd affiliated hospital of BUCM (ethical approval number BZYSY-2019KYKTPJ-04). This study will be performed according to the guidance and principles of the declaration of Helsinki. The authors retain full control of the manuscript content. The flowchart of this trial is shown in Figure 1.

**Figure 1 F1:**
[figure not shown]
Flowchart of the study.

### Participants

2.2

Participants will be recruited through multimodal strategies, including posters in the campus of BUCM and nearby 2 universities, and advertisements in social media (WeChat). The posters will contain brief introductions about the protocol of study, inclusion and exclusion criteria and the contact information of the researchers, who will enroll the patients. Every potential participant with interest in the study will contact the trial personnel and undergo a basic evaluation. Those who decide to participate, go through the preliminary evaluation, and provide written informed consent will undergo further examination and ultrasonography at the hospital. Finally, those who satisfy all the inclusion criteria will be enrolled. Participants will return on the first day of their next menstrual cycle for treatment when the pain level was confirmed to be ≥40 mm on the visual analog scale for pain (VAS-P) scale.

#### Sample size

2.2.1

In this study, the sample size was calculated according to following repeated measurement formula: 

Where N is the sample size of each groups, α is the significance level (0.05), β is related to study power (0.2) σ^2^ is the variance of measurements, δ is minimum effect size, *p* is the number of observations before treatment of each participant, *r* is the number of observations after treatment of each participant and ρ = 0.65. Based on our previous pilot study^[30]^ with the standard deviation of VAS-P values of 19.67 after 30 minute treatment and minimum clinical effective changes of VAS-P of 10 mm, we calculated that a sample size of 20 per group was a necessary to provide 80% power to detect a difference in the VAS-P value between two groups, considering a 20% drop-out rate, 24 participants are required per group.

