#### Primary outcome measure

2.6.1

The severity of dysmenorrhea will be measured by VAS-P, which is continuous quantitative variable varying from 0 mm (no pain) to100 mm (extreme pain). And it has some documented validity and reliability.^[35,36]^ Participants will be assessed by asking to rate the severity of their pain on a standard 100 mm VAS-P at baseline, 5 minutes after needling, 10 minutes after needling (needle removal), and 10 and 30 minutes after removing the needles.

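### As printed, 24 per group with 20% drop-out does not keep the stated 20 per group; the gap is at most one patient per group and can be closed by rewording

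*Protocol article*

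**What the plan says.** Section 2.2.1 of the protocol article uses a repeated-measures formula. Its stated inputs are a 5% level ("α is the significance level (0.05"), β of 0.2, a correlation of 0.65, a "standard deviation of VAS-P values of 19.67 after 30 minute treatment" and "minimum clinical effective changes of VAS-P of 10 mm". From these it concludes that "a sample size of 20 per group was a necessary to provide 80% power", and in the same sentence adds the allowance for losses: "considering a 20% drop-out rate, 24 participants are required per group". The Methods part of the abstract carries the matching total: "Forty-eight patients who meet inclusion criteria will be randomized in a ratio of 1:1".

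The section defines p and r as the numbers of observations before and after treatment but gives no values for them. It does not say whether the 5% level is one-sided or two-sided, and it does not state the inflation formula. The sample-size formula itself is not visible in the copy reviewed, which is not held against the plan.

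**The concern.** The sentence presents 20 as the number that must remain evaluable, 20% as the expected loss and 24 as the number to randomise. Any two of these fix the third, and the printed third does not agree. If 20 is a firm requirement, the trial falls just short of it at its own drop-out rate. Section 3.5 names small sample size as the main limitation, so the reader should be able to follow how 48 was reached and what loss it tolerates. At stake is the consistency of the sample-size statement and, at most, a marginal amount of power.

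**Working it through.** **Inputs.** From section 2.2.1: α = 0.05, power 80%, SD = 19.67 mm, δ = 10 mm, ρ = 0.65, 20 per group before losses, 20% drop-out, 24 per group after. From the abstract: 48 in total. From section 2.1: participants "will be randomly allocated in a ratio of 1:1".

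Assumed: a two-sided level, p = 1 and r = 4. The values of p and r are read from the pain-score schedule in section 2.6.1, which measures "at baseline, 5 minutes after needling, 10 minutes after needling (needle removal), and 10 and 30 minutes after removing the needles", that is, once before and four times after the start of treatment. The formula below is also an assumption: it is the baseline-adjusted form that uses the symbols the section lists.

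**Step 1: reproduce the plan's 20.**

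N = 2(z₁₋α/₂ + z₁₋β)² × SD²/δ² × [(1 + (r − 1)ρ)/r − pρ²/(1 + (p − 1)ρ)]

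- Bracket: (1 + 3 × 0.65)/4 − 0.65² = 0.7375 − 0.4225 = 0.315
- N = 2 × 7.849 × 386.9/100 × 0.315 = 19.13, rounded up to 20 per group. The plan's figure is reproduced.

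**Step 2: apply the drop-out to the printed 20.**

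- Needed to keep 20 after 20% loss: 20/(1 − 0.20) = 25 per group, 50 in total
- Left from 24 after 20% loss: 24 × 0.8 = 19.2 per group; from 48: 38.4, against 40
- Loss that 24 tolerates before falling below 20: 1 − 20/24 = 16.7%, that is, 4 of 24. A fifth loss leaves 19.

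**Step 3: ways in which 24 can arise.**

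- 20 × 1.2 = 24
- 19.13/0.8 = 23.9, rounded up to 24

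Both give the printed number. The second depends on the assumptions above. A one-sided 5% level with p = 1 and r = 2 also reproduces 20: the bracket is 0.825 − 0.4225 = 0.4025 and N = 19.26. There 19.26/0.8 = 24.07, which rounds up to 25.

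**Step 4: size in power.** Normal approximation, two-sided 5%, effective SD = 19.67 × √0.315:

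| Evaluable per group | Power |
|---|---|
| 19 | 79.7% |
| 19.2 | 80.1% |
| 20 | 81.7% |

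Against the stated 80%, 19 whole patients per group fall short by 80 − 79.7 = 0.3 points.

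**The case against.** The best defence is that 24 may be exactly right. With the two-sided level and the measurement schedule of section 2.6.1, the requirement before rounding is 19.13. Correct division by 0.8 gives 23.9 and hence 24, and the 19.2 expected completers exceed 19.13, with 80.1% planning power. On that account 20 is only the rounded figure for reporting, and nothing is short.

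This defence stands in part. It defeats a stronger reading that a reader might infer, namely that the plan made the familiar mistake of multiplying by 1.2 instead of dividing by 0.8. The article shows no inflation step, and the match with 20 × 1.2 does not establish one.

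The defence does not remove the inconsistency in the text. The article never prints 19.13. It gives 20 as the necessary number and applies the allowance in the same sentence, and from 20 the answer is 25. The route to 24 through the unrounded figure also needs values of p, r and sidedness that section 2.2.1 does not give.

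It can further be objected that the power figures assume a baseline-adjusted analysis, whereas section 2.8 names repeated-measures ANOVA without mentioning such an adjustment. That is fair: the figures describe power under the inferred planning formula, not under a confirmed analysis.

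**Conclusion.** The point holds as a small inconsistency in the printed figures: 20 needed, 20% lost and 24 randomised cannot all be true together. Its size is at most one patient per group (24 against 25, or 48 against 50 in total) and about 0.3 points of planning power if 19 remain in each group. The arithmetic on the printed integers needs no assumption. The power figures and the alternative route to 24 rest on the inferred formula, a two-sided level, p = 1 and r = 4.

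Two further conclusions would go too far. First, the documents do not show that 24 is wrong or that the trial is materially underpowered. The difference between 81.7% at 20 and 79.7% at 19 is mostly slack from rounding 19.13 up to 20, and the plan promises only 80%. Second, a calculation with the t distribution gives 77.5% at 19 per group, which looks worse, but on that basis 20 per group already gives 79.7% before any loss. It therefore does not isolate the drop-out step.

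**What to change.** Correct the wording of section 2.2.1 in one of two ways, depending on how 24 was obtained:

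- If 20 evaluable per group is the requirement, state that 24 per group keeps 20 evaluable at up to about 16% drop-out (4 of 24). The article gives no drop-out data to choose between 16% and 20%. However, randomisation follows the baseline assessments (section 2.3) and the last pain score comes 30 minutes after removal of needles kept in for 10 minutes, so a lower allowance is plausible.
- If the unrounded figure was inflated, state the requirement as about 19.1 per group, give p, r and the sidedness, and show the division by 0.8. Then 24 at 20% drop-out is consistent.

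Either change costs a figure or a sentence, adds no patients and leaves the total of 48 in the abstract unchanged. Only if both 20 evaluable and 20% drop-out are to be kept as firm figures would the number become 25 per group, 50 in total, at a cost of two more patients.

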#### Inclusion criteria

2.2.2

Participants will be eligible if they

(1)Are aged between 18 to 30 years old, normal menstrual cycle (28 ± 7 days) in the last 6 months,(2)Have diagnosed as PD,^[11]^(3)Have also diagnosed as cold-dampness stagnation pattern according to traditional Chinese medicine (TCM),^[34]^(4)Have scores 40 mm on 100 on the VAS and no oral administration of any analgesic 24 hours before trial, and(5)Provide written informed consent.

#### Exclusion criteria

2.2.3

Participants with any of the following conditions will be excluded:

(1)Secondary dysmenorrhea caused by endometriosis, uterine myomas and polyps, pelvic inflammatory disease,(2)Irregular menstrual cycle, lactation, asthma, severe and uncontrolled psychiatric disorders, life-threatening conditions (eg, sever cardiovascular, liver or kidney diseases),(3)History of receiving treatment for PD within the last 3 months,(4)Participants who is familiar or has previous information about acupuncture, and women who have no compliance for acupuncture treatment will also be excluded.

#### Withdraw criteria

2.2.4

Participants could withdraw from the study due to any reason at any time and will not affect the doctor's treatment. Participants who have developed severe adverse events will also withdraw from the study and will be monitored till its resolution.

### Randomization

2.3

Participants will be randomized to either the perpendicular needling group or transverse needling group by an independent statistician from BUCM using computer-generated random allocation sequence in SPSS 20.0 software (IBM, Armonk, NY, USA) in ratio of 1:1. The acupuncturist will contact the randomization center by telephone for the group allocation of the participants, who meet the eligibility criteria after signing an informed consent and completing all baseline assessments. This procedure will ensure adequate randomization concealment.

### Blinding

2.4

In this study, the acupuncturist cannot be blinded to group allocation due to the specific nature of intervention. But, participants, outcome assessors, data collectors and statisticians will be blinded throughout the study.

### Interventions

2.5

Acupuncture treatment will be implemented, when the participants VAS-P score of menstrual pain in the first day of menstruation is equal to or more than 40 mm. Both groups will be received an acupuncture treatment for 10 minutes at bilateral SP6 acupuncture points, after sterilizing the skin on the areas where the needles will be inserted, by using single-use sterile filiform needles of 0.30 × 40 mm (Zhongyan Taihe, Beijing Zhongyan Taihe Medical Instruments center, Beijing, China). In perpendicular needling group, the needles will be vertically inserted to SP6 bilaterally in a depth of 1 to 1.2 cun and will be manipulated by lifting-thrusting and twirling methods for 30 seconds to achieve proper needling sensation. In transverse needling group, the needles will be inserted to bilateral SP6 transversely 1 to 1.2 cun toward the abdomen without any manipulation to avoid needling sensation. The location of the acupoint and 2 needling techniques are shown in Figure 2.

**Figure 2 F2:**
[figure not shown]
Location of the acupoint and 2 needling techniques. A: Location of the SP6; B: Tube needling at SP6 transversely; C: Tube needling at SP6 perpendicularly. SP6 = Sanyinjiao.

The acupuncture treatments in both groups will be performed by the same acupuncturist with 10 years of clinical experience throughout the study, the room temperature will be kept 25°C and other influencing factors are prevented to avoid bias.

In this study, patients will be instructed to use Aspirin for pain relief, if VAS pain be more than 80 mm.

### Outcome measures

2.6

The primary outcome measure is VAS-P, and secondary outcome measures are color doppler ultrasonography, Hamilton anxiety scale (HAM-A), the changes of blood pressure (BP) and heart rate (HR), and adverse events.

#### Primary outcome measure

2.6.1

The severity of dysmenorrhea will be measured by VAS-P, which is continuous quantitative variable varying from 0 mm (no pain) to100 mm (extreme pain). And it has some documented validity and reliability.^[35,36]^ Participants will be assessed by asking to rate the severity of their pain on a standard 100 mm VAS-P at baseline, 5 minutes after needling, 10 minutes after needling (needle removal), and 10 and 30 minutes after removing the needles.

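### The stated 20 per arm holds only under a baseline-adjusted analysis, which section 2.8 does not name; a second pre-treatment VAS-P mark would add power cheaply

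*Protocol article*

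**What the plan says.** Section 2.2.1 (Sample size) uses a repeated-measurement formula in which p "is the number of observations before treatment of each participant" and r is the corresponding number after treatment. The values of p and r are not printed. The printed inputs are "α is the significance level (0.05"), β of 0.2, a "standard deviation of VAS-P values of 19.67 after 30 minute treatment", a "minimum clinical effective changes of VAS-P of 10 mm" and a single correlation, "of each participant and ρ = 0.65". The result is that "a sample size of 20 per group was a necessary to provide 80% power", raised to 24 for drop-out.

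Section 2.6.1 lists the VAS-P times in full: participants "rate the severity of their pain on a standard 100 mm VAS-P at baseline, 5 minutes after needling", then at needle removal and 10 and 30 minutes after removal. That is one reading before needling and four after.

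Section 2.2 has women return for treatment on the first day of the next cycle "when the pain level was confirmed to be ≥40 mm on the visual analog scale for pain", and section 2.5 repeats this condition. Neither section says whether this entry mark is the baseline of section 2.6.1 or a separate mark.

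Section 2.3 places the allocation call after all baseline assessments. Section 2.8 plans repeated measures ANOVA for variables measured at several times and names no baseline covariate. Section 3.5 gives the small sample as the main limitation.

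**The concern.** The sample size formula takes credit for the pre-treatment reading, while the analysis section does not say how that reading enters the comparison of arms. It could be a covariate, one of the repeated levels, or unused. The power at 20 per arm depends heavily on which of these is meant.

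A VAS-P mark is also required on the treatment day to open treatment. If it is distinct from the baseline, it is a pre-treatment reading that the article gives no further use. If it is the baseline, one more mark before allocation would supply a second. Either way, a trial that calls its size its main limitation can gain precision on its primary outcome without recruiting anyone.

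**Working it through.** **Inputs.** From section 2.2.1: α 0.05, power 0.80, SD 19.67 mm, difference 10 mm, ρ 0.65. From section 2.6.1: p = 1 and r = 4. Assumptions: a two-sided test (sidedness is not printed with α), equal variances, and ρ common to all pairs of readings unless stated otherwise. ρ_bb denotes the correlation between two pre-treatment marks; the article does not give it.

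**Formula.** n per arm = 2(1.96 + 0.8416)² × (19.67/10)² × F = 60.74 × F, where F depends on how baseline is used:

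- baseline-adjusted: F = [1 + (r − 1)ρ]/r − pρ²/[1 + (p − 1)ρ_bb]
- change from baseline: F = [1 + (r − 1)ρ]/r + [1 + (p − 1)ρ_bb]/p − 2ρ
- post-treatment mean only: F = [1 + (r − 1)ρ]/r

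Power at 20 per arm is Φ(10/(19.67 × √(2F/20)) − 1.96).

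**Reproducing the stated 20.** With r = 4 the first term is (1 + 3 × 0.65)/4 = 0.7375. Baseline-adjusted with p = 1: F = 0.7375 − 0.4225 = 0.3150, so n = 60.74 × 0.3150 = 19.13, rounded up to 20. This matches. The combination p = 2, r = 2 also gives 20 (19.00) but does not fit the schedule in section 2.6.1. A one-sided test with p = 1, r = 4 gives 15.07 and does not match.

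**Dependence on the analysis (p = 1, r = 4).**

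| Use of baseline | F | n per arm | Power at 20 per arm |
|---|---|---|---|
| Covariate | 0.3150 | 19.13 | 81.7% |
| Change score | 0.4375 | 26.57 | 68.1% |
| Not used | 0.7375 | 44.79 | 46.5% |

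**Adding a second pre-treatment mark (p = 2, r = 4, baseline-adjusted).** Pre-post and post-post correlations stay at 0.65. Example at ρ_bb = 0.65: F = 0.7375 − 2 × 0.4225/1.65 = 0.2254.

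| ρ_bb (assumed) | F | n per arm | Power at 20 per arm |
|---|---|---|---|
| 0.65 | 0.2254 | 13.69 | 92.3% |
| 0.85 | 0.2807 | 17.05 | 85.9% |
| 0.90 | 0.2928 | 17.78 | 84.4% |
| 0.95 | 0.3042 | 18.47 | 83.0% |
| 1.00 | 0.3150 | 19.13 | 81.7% |

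**Comparison with a fifth post reading (p = 1, r = 5).** F = (1 + 4 × 0.65)/5 − 0.4225 = 0.2975, so n = 18.07 and power is 83.8%. A second baseline equals this when 0.845/(1 + ρ_bb) = 0.7375 − 0.2975 = 0.44, that is at ρ_bb of about 0.92.

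**The case against.** The strongest reply is that nothing here is wrong. The stated 20 is right for the schedule as written, the 80% target is met on the protocol's own formula (81.7% at 20 per arm, 88.1% if all 24 are analysed), and naming a small sample as a limitation does not admit a lack of power. This stands. A reader might infer from the 68% and 46% figures that the trial is underpowered. The article does not support that, because section 2.8 does not rule out baseline adjustment and a fuller analysis plan may specify it.

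It is also fair to object that two untreated marks on the same day may correlate well above 0.65. The gain is then small: 1 to 3 points at 0.90 to 0.95. This also stands, so the range has to be carried up to 1.0.

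Two further readings are tempting and do not hold:

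- **That a second baseline is worth far more than another post-treatment reading.** This is true only at lower correlations. The two are equal at about 0.92, and beyond that the post reading is worth more.
- **That the extra mark frees the baseline from selection at 40 mm.** Averaging with the entry mark only dilutes the selection. Sections 2.2, 2.3 and 2.5, read together, put both marks before allocation, so any truncation or regression to the mean affects both arms alike and does not bias their comparison.

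Finally, Table 1 is not available in the text at hand and might show whether the entry mark and the baseline are separate. Section 2.6.1 nevertheless lists the VAS-P times completely, and the remedy works in either case.

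**Conclusion.** The point holds as an optional gain in efficiency. The sample size is not in error. It does rest on baseline adjustment that section 2.8 leaves unnamed, and this matters more than the number of baseline marks: at 20 per arm, power is 82% with adjustment, 68% with change scores and about 46% with baseline ignored. Given adjustment, a second pre-treatment mark adds between 0 and about 10 percentage points, according to a correlation the article does not supply. Without any use of baseline it adds nothing. All these figures assume a two-sided 0.05 test, SD 19.67 mm, a 10 mm difference and correlations of 0.65 among the other readings.

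**What to change.** 1. In section 2.8, state that post-treatment VAS-P is compared between arms with adjustment for the pre-treatment readings. Fix in advance whether their mean or both marks enter as covariates.
2. In section 2.6.1, say whether the entry mark and the baseline are the same. Record the entry mark as data, and take one separate VAS-P mark after the other baseline assessments (Doppler, HAM-A, blood pressure and heart rate) and before the allocation call of section 2.3.
3. In section 2.2.1, print the values of p and r used. As ρ_bb is unknown, the second mark is better held as a reserve of power than used to reduce the 24 per arm.

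The entry rule is unchanged. The cost is one VAS mark taking seconds, one CRF field per woman, and a commitment to a baseline-adjusted model; no extra women or visits are needed.
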